## Abstract

**Background:**

The importance of insulin resistance is gaining increasing attention as it plays an important role in carcinogenesis in hepatocellular carcinoma (HCC). Although exercise is the most important intervention for lowering insulin resistance, it is not easy for HCC patients to maintain high compliance and do appropriate exercise. Mobile health (mHealth) with wearable devices can be the solution to carry out an adjusted and supervised exercise that can normalize insulin resistance in patients with HCC. We developed an HCC-specific application equipped with patient-centered exercise. In this paper, we present a randomized controlled trial protocol comparing an intervention group with a control group to determine whether mHealth-based exercise is effective in normalizing insulin sensitivity in HCC patients with insulin resistance after anticancer treatment.

**Methods:**

An assessor unblinded open label randomized controlled trial (RCT) will be conducted for 80 participants with treatment-naïve or recurrent HCC who have received treatment and achieved complete response at the time of screening. They will be randomly assigned (1:1) to one of two groups: an intervention group (*n* = 40) and a control group (*n* = 40). The intervention group will carry out mHealth-based exercise for 6 months from baseline, whereas the control group will receive the usual follow-up care for the first 3 months and mHealth-based exercise for the next 3 months. Both groups will be assessed at baseline, 3 months, and 6 months from baseline. The primary outcome is the normalized rate of insulin resistance in each group at 3 months. Insulin resistance is estimated by calculating homeostatic model assessment for insulin resistance (HOMA-IR). The secondary outcomes are body composition, physical fitness level, physical activity, and quality of life at 3 months.

**Discussion:**

This study is the first RCT to investigate the effect of mHealth-based home exercise with a wrist-wearable device on insulin sensitivity, physical fitness, and quality of life for HCC patients with insulin resistance. The result of this RCT will confirm not only safety and functional improvement but also biological effect when exercising using mHealth in HCC patients.

**Trial registration:**

ClinicalTrials.gov NCT04649671. Registered on 2 December 2020. The World Health Organization Trial Registration Data Set is not registered.

**Supplementary Information:**

The online version contains supplementary material available at 10.1186/s13063-022-06858-w.

## Introduction

The growing interest in the association between exercise and cancer has led to an increase in research on this topic. It is proven that exercise has a preventive effect in seven types of cancer (colon, breast, endometrial, kidney, bladder, esophagus, and stomach) and improves survival in three types of cancer (breast, colon and prostate) [1, 2]. In addition, there is sufficient evidence that exercise improves common cancer-related health outcomes in a variety of cancers, including anxiety, depressive symptoms, fatigue, physical functioning, and health-related quality of life [3]. However, little is known about the role of exercise for patients with hepatocellular carcinoma (HCC), which has the 4th highest mortality rate of all cancers [4].

Viral hepatitis in the East and alcohol or fatty liver/metabolic disease in the West are major risk factors for HCC. Fatty liver and metabolic diseases are currently changing as the major risk factors for HCC as westernization progresses and are expected to increase gradually [5]. Insulin resistance is one of the main mechanisms by which fatty liver and metabolic diseases cause HCC, and several studies have found a link between insulin resistance and HCC independent of viral hepatitis [6]. Kim et al. revealed that the incidence of HCC in patients with insulin resistance was significantly higher in multivariate analysis with hazard ratio of 3.24 (95% confidential interval 1.13–9.31) compared to patients without insulin resistance [7]. Similarly, Imai el al. also confirmed that the risk of HCC recurrence was significantly higher in patients with insulin resistance compared to patients without insulin resistance in multivariate analysis, with a hazard ratio of 1.48 (95% confidential interval 1.03–2.13) [8]. Therefore, it is necessary to treat insulin resistance in patients with a previous history of HCC, and the most basic and essential treatment for insulin resistance is exercise and diet [9]. In fact, animal studies have demonstrated the positive influence of moderate physical activity on HCC growth and progression [10, 11]. And a prospective cohort study suggested an inverse association between physical activity and the risk of HCC [12].

Exercise is expected to have a positive effect on patients with HCC, but patients and doctors consider hepatic decompensation to be a risk when exercising [13]. Only a few studies have reported the positive effects of in-hospital exercise for HCC patients [14–16]. Longer-term exercise interventions are necessary, especially for cancer patients, but it is not practical for all interventions to be carried in hospitals. Digital health, especially mobile health (mHealth) with wearable devices, is a promising solution that can allow patients with HCC to carry out adjusted and supervised exercise. The usefulness and effectiveness of mHealth has been reported for several cancers, such as breast [17] and prostate [18] cancer. Our previous study presented the efficacy and safety of the mHealth application and wearable devices, and their physical performance for patients with HCC. Our surveillance system, consisting of wearable Internet of Things (IoT) devices and HCC specific application, showed no complications or biochemical deterioration and showed an improved physical performance during the 12-week intervention period [19]. However, the biological improvement of insulin resistance was not confirmed, there was no control group for comparison, and the exercise intensity was manually readjusted once. Hence, we modified the HCC-specific application with monitored patient-centered exercises, and we planned a randomized controlled trial (RCT) using this application. The intervention group will carry out with mHealth-based exercises for 6 months and the control group will receive usual follow-up care for the first 3 months and mHealth-based exercise for the following 3 months.

Our hypothesis is that insulin resistance will be more significantly normalized, and physical fitness and quality of life (QoL) will be improved more significantly in the intervention group using the mobile application and exercise program for HCC patients than in the control group. This paper presents an open label 1:1 randomized controlled trial protocol comparing intervention and control groups to determine the effect of *m*Health-based exercise on *I*nsulin *S*ensitivity for patients with *H*CC and insulin resistance (mISH) after anticancer therapy.

## Methods/design

### Study design

This protocol is a two-arm, open-label RCT that compares usual follow-up care with mISH from baseline to 3 months. Participants will be collected in one academic hospital (Samsung Medical Center, South Korea).

### Study procedure

Figure 1 outlines the flowchart of the RCT and Table 1 indicates the summary of baseline screening, enrollment, and assessment during study visits. The patients with treatment-naïve and recurrent HCC who have received treatment and achieved complete response at the time of screening will be screened about general condition, alcohol intake history, liver function, medical history, and drug history. A written consent including collection and use of participant data and biological specimens will be obtained from the participant by physician investigator.

**Fig. 1 Fig1:**
[figure not shown]
Participant flow through the randomized controlled trial. RFA, radiofrequency ablation; HOMA-IR, homeostatic model assessment for insulin resistance; 6 MWT, 6-min walk test; IPAQ-SF, Korean version international physical activity questionnaire-short form; EORTC-QOL-C30, European organization for research and treatment of cancer quality of life questionnaire C30; MNA, Mini nutritional assessment

**Table 1 Tab1:**
[figure not shown]
Summary of baseline screening, enrollment, and assessment during study visits

*mHealth* mobile health, *IPAQ-SF* International Physical Activity Questionnaire-Short Form, *EORTC-QLQ-C30* European Organization for Research and Treatment of Cancer-Quality of Life Questionnaire

The consent form states whether the participant consents to the use of data or if he or she chooses to withdraw from the trial. Because information obtained from blood tests is included in the outcomes of this study, consent for human material is also obtained. Informed consent materials are available from the corresponding author on request.

Homeostatic model assessment for insulin resistance (HOMA-IR) will be assessed in those who consented. Among screened participants, only patients with insulin resistance (HOMA-IR ≥ 2.2) will be enrolled in outpatient clinic. After enrollment, they need to be randomized based on 1:1 allocation to two groups: the intervention group should carry out mISH for 6 months, and the control group should receive the usual care for the first 3 months and mISH for the next 3 months. Participants should continue to take medications for other conditions as normal. In addition, the individual’s additional physical activity is not restricted. In both groups, assessments for the primary and secondary outcomes will be performed after 3 and 6 months from baseline.

After 3 months of usual care, 3 months of intervention was provided to the control group to avoid ethical issues. The randomized controlled trial design in this study is limited to comparing the outcomes at 3 months of the intervention group and the control group. The reason for planning the assessment of the outcomes at 6 months is to compare the outcomes at baseline, 3 months, and 6 months within the intervention group, and to compare the period of usual care with the period of intervention within the control group.

### Allocation, randomization, and blinding

Participants will be randomly assigned to the intervention group (*n* = 40), receiving 12 weeks of mISH or to the control group (*n* = 40), not receiving mISH, in a 1:1 ratio. Block randomization with an allocation ratio of 1:1 is implemented. The baseline assessments will be performed after allocation and randomization. During the study, the assessor has no choice but to see the participant wearing the wearable device (Dofit), and an open-label study will be conducted with assessors not being blinded.

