### Assessments and data collection methods

Assessments, such as blood test (fasting glucose, insulin, hemoglobin A1c and lipid profile), physical activity, and QoL questionnaires, and physical fitness assessments will be carried out at baseline and 3 and 6 months after baseline. A nutritional assessment will be done to determine if there are any nutritional differences between the two groups. Table 1 describes the assessments for each time point.

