#### Primary outcome

The primary outcome is the normalized rate of insulin resistance in each group at 3 months. Insulin resistance is estimated by calculating HOMA-IR, which uses the computer-based solution of the model provided by the Diabetes Trials Unit, Oxford Center for Diabetes, Endocrinology, and Metabolism (http://www.dtu.ox.ac.uk/homa). When the HOMA-IR falls below 2.2, it is considered that insulin resistance is normalized.

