### Statistical analysis

The strategy for statistical analysis is developed under the supervision of a biostatistician at the Samsung Medical Center. Analyses will be performed using an intention-to-treat approach. Descriptive statistics will be used to present baseline characteristics of both groups. For the primary outcome, the proportion of participants in each group with normalized HOMA-IR at 3 months after baseline will be compared using the chi-square test. For the secondary outcomes, changes in blood test (fasting glucose, insulin, hemoglobin A1c and lipid profile), body composition (muscle mass, body fat), physical fitness level (grip strength test, 30 s chair stand test, 6 MWT), physical activity (IPAQ-SF), general health-related quality of life (EORTC-QLQ-C30), and adverse events at 3 months after baseline will be compared by an unpaired *t*-test. In the control group, according to the self-controlled study design, all outcomes after 3 months of usual care and after using mISH for 3 months will be compared by paired *t*-test. In the intervention group, the primary and secondary outcomes of baseline, 3 months, and 6 months of intervention will be analyzed with repeated measured ANOVA to check whether there are significant changes over time. All tests will use a 5% level of significance (*p* < 0.05). Relative risks and 95% confidence intervals are reported for primary outcome.

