## Oversight and monitoring

### Composition of the coordinating center and trial steering committee

There is no coordinating center or study steering committee in this study. This study is conducted in a single center without funding. Gastroenterology research team who enrolls participants and Rehabilitation medicine research team is responsible for patient evaluation and intervention management meet regularly to evaluate the performance and progress of the study and ensure that the study protocol is followed. The entire research team, including the two principal investigators, meets every 3 months to discuss the management and financial issues related to the study. To ensure that the protocol is implemented as planned, the principle investigators are responsible for managing and overseeing the study and providing guidance and administrative support.

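### Baseline is measured after randomization by unblinded assessors, which exposes the change scores of the effort-dependent and self-reported secondary outcomes to knowledge of the allocation

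*Protocol article*

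**What the plan says.** Four parts of the protocol article bear on this point.

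- **Order and blinding** (Allocation, randomization, and blinding): "The baseline assessments will be performed after allocation and randomization". The same section says that "an open-label study will be conducted with assessors not being blinded", because the assessor cannot avoid seeing the wearable.
- **What is measured at baseline** (Assessments and data collection methods): besides blood tests, "physical activity, and QoL questionnaires, and physical fitness assessments will be carried out at baseline and 3 and 6 months after baseline".
- **How it is analysed** (Statistical analysis): "For the secondary outcomes, changes in blood test (fasting glucose, insulin, hemoglobin A1c and lipid profile), body composition (muscle mass, body fat"), followed by fitness, IPAQ-SF, EORTC-QLQ-C30 and adverse events. These changes "at 3 months after baseline will be compared by an unpaired" t-test.
- **Who measures** (Composition of the coordinating center and trial steering committee): the "Rehabilitation medicine research team is responsible for patient evaluation and intervention management".

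Two further statements limit the point. HOMA-IR is obtained after consent and before randomization (Study procedure, text after Table 1): "Among screened participants, only patients with insulin resistance (HOMA-IR ≥ 2.2) will be enrolled in outpatient clinic". The primary outcome is a status at 3 months, not a change: "When the HOMA-IR falls below 2.2, it is considered that insulin resistance is normalized".

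**The concern.** Randomization makes the arms comparable in everything measured before the allocation can have an influence. A baseline taken afterwards loses that guarantee when participant and assessor can know the arm. A participant told to wait 3 months may push less hard in a walk test. One about to start an exercise programme may push harder, or may rate present activity and well-being differently. An assessor from the team that runs the intervention may encourage unevenly without meaning to.

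Because the planned analysis subtracts this baseline, a difference between arms created at baseline is read as a difference in change over 3 months. At stake are the comparisons of physical fitness, physical activity and quality of life. Fitness and quality of life are part of the stated hypothesis in the Introduction. The within-arm analysis of the intervention group over baseline, 3 and 6 months uses the same baseline. The baseline 6-minute walk also enters the setting of initial exercise intensity for some participants (Exercise management), so a shifted value would carry into delivery of the intervention.

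**Working it through.** **1. The plan's own figure, and whether it is touched.** Inputs from Sample size calculation: 30% v 5%, 80% power, 5% significance, 10% dropout. With a two-sided test, pooled variance and no continuity correction:

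n = [1.960·√(2·0.175·0.825) + 0.842·√(0.30·0.70 + 0.05·0.95)]² / 0.25² = (1.053 + 0.427)² / 0.0625 ≈ 35.1, so 36 per group; 36/0.90 = 40.

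The stated 36 and 40 are reproduced. They rest on a 3-month proportion compared by chi-square, with no baseline subtracted, so the order of baseline and allocation does not alter them.

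**2. How a baseline shift enters a change score.** Let b be the between-arm shift caused by knowing the allocation at baseline, and f the corresponding shift at the unblinded 3-month visit. With no true effect, the expected difference in change is f − b. If the shift persists fully (f = b) it cancels. If it has gone (f = 0) it enters in full. Only the net part matters.

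**3. Effect on the rejection rate.** Write d for the size of the net shift in standard errors of the difference in change. The two-sided 5% test rejects with probability P(|Z + d| > 1.96):

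- d = 0: 5%
- d = 0.75: P(Z > 1.21) + P(Z < −2.71) = 0.113 + 0.003 = 0.117
- d = 1.5: P(Z > 0.46) + P(Z < −3.46) = 0.323 + less than 0.001 = 0.323

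These rejections are almost all in one direction. At d = 0.75 about 11.3 of the 11.7 percentage points lie on the side of the net shift, and the other side falls from 2.5% to about 0.3%.

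**4. What such shifts mean in units.** The documents give neither a standard deviation nor a correlation for any secondary outcome, so both are assumed here.

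- 6-minute walk, assumed SD of change 60 m, 40 per arm: SE = 60·√(2/40) = 13.4 m. Then d = 0.75 is about 10 m and d = 1.5 about 20 m.
- Any outcome in baseline SD units, 36 per arm, baseline/follow-up correlation ρ: SE = √(2(1−ρ))·√(2/36). Rejection rates under no effect:

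| Net shift (SD) | ρ = 0.5 | ρ = 0.7 | ρ = 0.8 |
|---|---|---|---|
| 0.1 | 7.1% | 8.5% | 10.3% |
| 0.2 | 13.6% | 19.5% | 26.9% |
| 0.3 | 24.7% | 37.6% | 52.1% |
| 0.5 | 56.4% | 78.2% | 91.8% |

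If half of a 0.2 SD baseline shift persists at 3 months, the net shift is 0.1 SD and the first row applies.

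**5. Whether analysis could repair it.** Adjusting for the same shifted baseline, with no shift left at 3 months, gives a bias of ρb and a residual SD of √(1−ρ²). At ρ = 0.7 the rejection rate is 13.2% for b = 0.2 SD and 23.9% for b = 0.3 SD. That is lower than with change scores but above 5%. The protocol plans t-tests, so this only shows that a later change of analysis would not fully remove the problem.

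**6. Whether the order is needed.** Eligibility by HOMA-IR is settled before randomization. The reason given for unblinding is that the band is seen during the study; before allocation there is no arm to reveal. Nothing in the text shown requires baseline to come second.

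**The case against.** The strongest reply is that the main result is untouched. The primary outcome is a laboratory-based status at 3 months, compared as proportions, and entry HOMA-IR is measured before randomization. This stands in full. A reader might infer from a post-allocation baseline that the primary comparison is biased; the documents do not support that.

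Second, a reader might infer that every change-score outcome is compromised. The timing is indeed common to all of them, but the exposure is not. Blood tests and bioimpedance are hardly open to an assessor's influence and could move mainly through behaviour between allocation and baseline. HbA1c would barely respond. Glucose and insulin also have a pre-randomization screening value, although the protocol does not say whether it serves as baseline.

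Third, a reader might infer false claims of benefit. Disappointment in the control arm and motivation in the intervention arm would raise the intervention baseline relative to control, and so hide benefit. The opposite pattern is also possible, and the documents do not settle which applies. The same people are unblinded at 3 months, so part of a shift may cancel. Both points stand and are why only a net shift is claimed.

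Fourth, the protocol does not say when the allocation is disclosed to participant and assessor, and Fig. 1 and Table 1 are not shown. It remains possible that disclosure is delayed, but the text is explicit about the order and describes no such safeguard.

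Finally, it is tempting to add that taking off the wrist band would blind the assessors. That is a separate matter of follow-up blinding, and it would not reliably blind a team that also manages the intervention.

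**Conclusion.** The point holds for grip strength, 30-s chair stand, 6-minute walk, IPAQ-SF and EORTC-QLQ-C30. Their baselines are taken when the arm can be known, by unblinded assessors from the team responsible for the intervention, and the planned comparison subtracts those baselines. The size and direction of any shift are unknown. The figures above rest on assumed net shifts, an assumed 60 m SD and assumed correlations, and show sensitivity rather than an estimate of bias. On those terms, a net shift of 0.75 standard errors takes the rejection rate under no effect from 5% to about 12%, and 1.5 standard errors to about 32%. The sample size and the primary test are unaffected. This should be fixed, because the exposure is avoidable and cannot be fully repaired in the analysis; it is not a fault that invalidates the trial.

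**What to change.** Change the sentence on order in Allocation, randomization, and blinding. For all participants not yet randomized, baseline assessments should be completed after HOMA-IR eligibility is confirmed and before the allocation is generated or disclosed. Make the same change wherever the visit schedule sets out the order.

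The trial started in March 2021 (Trial status), and under the current text everyone already randomized has a post-allocation baseline. For them, report this order as a limitation of the change-score comparisons. A before/after sensitivity analysis among those participants alone would have nothing to contrast. If enough participants are later randomized under the new order, compare the results by order.

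The sample size stays at 36, inflated to 40 per group. The cost is small but not nil: a few participants may be assessed and then not randomized, and the enrolling Gastroenterology team and the evaluating Rehabilitation team must coordinate the sequence of steps. Because the visit schedule is not shown, it cannot be confirmed that the new order fits into existing visits.

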### Participants

A total of 80 participants will be included in the study, 40 each in the intervention and control groups.

#### Inclusion criteria

Adults aged 20–70Early-stage HCC, defined by modified International Union Against Cancer (UICC) stage 1 or 2Participants with treatment-naïve and recurrent HCC who have received treatment and achieved complete response at the time of screeningInsulin resistance (homeostatic model assessment for insulin resistance (HOMA-IR) ≥ 2.2)Eastern Cooperative Oncology Group (ECOG) performance status of 0–2

